# The feasibility and impact of instrument-assisted manual therapy (IAMT) for the lower back on the structural and functional properties of the lumbar area in female soccer players: a randomised, placebo-controlled pilot study design

**DOI:** 10.1186/s40814-020-00592-3

**Published:** 2020-04-16

**Keywords:** Instrument-assisted, Myofascial, Randomised placebo-controlled, Thoracolumbar fascia, Shear motion, Athletes, Ultrasound, Manual treatment

## Abstract

**Background:**

Myofascial (self-)treatments, such as foam rollers to therapeutic instruments in manual therapy, are utilized increasingly in prevention and therapy in healthy people, athletes, and patients suffering from chronic back pain. However, there is limited knowledge about the effectiveness of treatment and the underlying mechanisms of myofascial therapies, especially for instrument-assisted manual therapy (IAMT). Therefore, this pilot study will investigate the feasibility and impact of IAMT for the lumbar area compared with heat application and placebo treatment as a basis for calculating the sample size for further full studies. The primary outcomes will be a critical analysis of the feasibility of the measurement protocol in terms of time economy and expressiveness and of the short- and long-term effects on shear motion of the single tissue layers of the lower back obtained through ultrasound imaging. Secondary outcomes will include thickness and compressibility of the lumbar structures and flexibility of the dorsal structures, indentometry, and superficial skin temperature.

**Methods:**

A minimum of 60 healthy, competitive 15–35-year-old female soccer players will be recruited and randomised into three groups. Short-term effects of IAMT on thoracolumbar structures will be compared with heat application and pressure-less placebo treatment. Long-term effects in the IAMT group will be tested after nine further interventions over a 5-week period (2×/week) and compared with the placebo group, which will not receive further treatments but will serve as a control. Intermediate and final testing of both groups will occur in weeks three and five.

**Discussion:**

This pilot study will assess the feasibility and the impact of IAMT for the lower back particularly by examining the structural and functional properties of myofascial tissue using diagnostic ultrasound. These outcomes could evaluate the feasibility of the measurements used, shall build a basis for sample size calculation of further full studies, and might generate a greater understanding of myofascial therapies, especially IAMT, for the lower back and its benefits. If this approach proves to be practicable, next steps will be further full studies with soccer players, other sports, and patients with low back pain.

**Trial registration:**

German Clinical Trials Register (DRKS00012252) 20.06.2018; retrospectively registered.

## Background

Besides transmitting muscle force, providing structural integrity, and interconnecting the human body and its internal organs [1–4], fasciae have a variety of complex functions. For instance, since the discovery of intrafascial free nerve endings, and Pacini as well as Ruffini corpuscles, fascia is held jointly responsible for nociception and proprioception [5–7]. Further, myofibroblasts and contractile activities have also been observed in fasciae [8]. Because of these various findings, fasciae are increasingly becoming the focus of scientific research in terms of musculoskeletal disorders such as low back pain, which presents one of the most important and cost-intensive complaints [9–12]. In this context, the thoracolumbar fascia plays a central role because it serves as both a pivot and an anchor. It connects the core with the extremities through three different tissue layers [13, 14], and it links the right side with the left side of the body through its crossing fibres [13, 15–17]. Through its connections with the musculi (Mm.) transversus abdominus and obliquus internus, it also acts from the paravertebral muscles down to the deep abdominal muscles [18].

Up to now, most results have come from studies of patients with chronic back pain, in which ultrasound imaging showed structural changes and significant decreases in shear motion of the thoracolumbar fascia [19, 20]. These changes were associated with a negative impact on the mechanical and receptor properties of the fascial tissue, and they may be responsible for limited mobility and flexibility [19–21]. Ultrasound imaging allows an analysis of structural changes like soft tissue consistency and compressibility compared with the established more selective but only mechanical indentometry measurement developed by Fischer [22, 23].

In healthy subjects, Griefahn et al. [24] found a significant increase in shear motion of the thoracolumbar fascia after a single treatment of the Mm. gluteus maximus, latissimus dorsi, and erector spinae with a foam roller in a placebo-controlled trial. Furthermore, the use of foam rollers and massage sticks has been shown to increase the maximum range of motion [25–27], improve vascular functionality [28], and reduce pain without compromising the development of strength, particularly in athletes [25, 26, 29]. In addition to these myofascial (self-)treatments, instrument-assisted manual therapy (IAMT) of the myofascial tissues is being increasingly implemented in usually prescribed regimes of 5 to 10 treatments. For this type of treatment, the therapist applies an appropriate amount of pressure on the myofascial tissue. Specific tools enable the therapist to reach the deeper layers of the tissue and target a more precise or extensive area. This kind of therapy is supposed to increase range of motion and functionality because of improved blood flow accompanied by increased tissue temperature, pain reduction as well as generated pressure, tensile, and shear forces. However, the underlying mechanisms behind these processes are still unknown, but increased microcirculation and altered expression of cytokines in the ground substance, particularly growth factors and inflammatory mediators that enhance regeneration and wound healing, are discussed [21, 30–32].

Through modern diagnostic ultrasound, novel and highly promising findings of both the structural and functional aspects of IAMT are anticipated to provide a greater understanding of its tissue effects.

## Aims

Therefore, this pilot study aims to investigate the feasibility and the impact of IAMT for the lumbar area on the structural and functional properties of the myofascial tissue of the lower back and adjacent motion segments in healthy female soccer players as a reference for sample size calculation of further full studies.

The primary outcomes will be a critical analysis of the time economy and expressiveness of the used measurement methods in terms of quality and quantifiability as well as the effect of IAMT on shear motion of the lumbar structures (subcutaneous tissue, fascia, and musculus (M.) erector spinae) obtained through ultrasound imaging and compared with heat application (short-term) and placebo treatment (short-term and long-term). Secondary outcomes will include thickness and compressibility of the lumbar structures as well as flexibility of the dorsal structures, mechanical tissue deformation resistance (indentometry), and superficial skin temperature. Further secondary outcomes will be the subjectively perceived flexibility and state of the lower back.

## Methods

### Study design

This randomised placebo-controlled pilot study will evaluate the feasibility of the planned measurements and generate the first information about the underlying effects of IAMT on structural and functional tissue properties of the lower back as recently reported in a pre-existing study on the lower leg [32]. Subjects will be recruited by a person who is not involved in the testing. The participants will be randomised into three even groups (1:1:1) using an adaptive biased-coin design (urn design), and they will receive an anonymised participant ID. The intervention group (IAMT group) will receive a standardised IAMT on the lumbar area. The comparison group (heat group) will receive heat therapy through an applied heat source, whereas the third group (placebo group) will undergo a pressure-less placebo treatment using an ultrasound transducer. All treatments will be performed once on the right side of the lower back by the same therapist. Testing, using a standardised protocol, will be conducted immediately before, immediately after, and 45 min after the treatment by a blinded investigator who is not involved in the treatments. The long-term evaluation will start with the first treatment, after which the IAMT group will receive nine further IAMT interventions twice a week over a five-week period, as usually practised in Germany, with a minimum of 48 h between treatments. The long-term effects of the IAMT will be controlled by the placebo group, which will be tested regularly over the 5-week period but not treated any more after the initial treatment and will act as a control group for the long-term effects of IAMT from this timepoint. Intermediate and final testing will be performed in weeks three and five, and a short questionnaire about subjectively perceived changes of flexibility and state of the lower back, as well as deviations in frequency and duration of the weekly training schedule, will be distributed before every intervention (Figs. 1 and 2).

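### As worded, the follow-up questionnaire is tied to interventions, so the long-term control group has no stated follow-up on perceived outcomes or training deviations

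*Protocol article*

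**What the plan says.** All references are to the protocol article.

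- **Outcome status (Aims).** "Further secondary outcomes will be the subjectively perceived flexibility and state of the lower back".
- **Instrument (Study design).** Follow-up uses "a short questionnaire about subjectively perceived changes of flexibility and state of the lower back". The same form also asks about training, and its timing is stated in these words: "deviations in frequency and duration of the weekly training schedule, will be distributed before every intervention". The sentence refers the reader to Figs. 1 and 2.
- **Sessions (Study design).** After the first treatment "the IAMT group will receive nine further IAMT interventions twice a week over a five-week period". The placebo group, which serves as the long-term control, is "tested regularly over the 5-week period but not treated any more after the initial treatment". The heat group is treated once and has no part in the long-term evaluation.
- **Test visits (Abstract, Methods).** "Intermediate and final testing of both groups will occur in weeks three and five".
- **Baseline (Measurements).** A questionnaire before the first treatment records perceived flexibility, the state of the lower back and training sessions in all three groups, so that group differences can be identified. The ordered list of tests that follows covers skin temperature, indentometry, the ultrasound measures and flexibility. It contains no questionnaire.

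**The concern.** The rule that triggers the form is an intervention, and the two groups in the long-term comparison differ in exactly that respect. A form that follows the treatment schedule goes to the treated group throughout and stops for the control group after its only session.

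Two things are at stake. First, the perceived outcomes are self-reports, where expectation and attention can act strongly. The Discussion hopes to learn about the perceived effects of IAMT. Without follow-up forms from the control group, a change in the IAMT group can be described but not set against what players report over the same five weeks without further treatment. Second, these are competitive players whose training may vary over five weeks. If deviations are recorded in one group only, a difference in training between the long-term groups cannot be examined. Neither gap can be closed by a later analysis, because the data would not exist.

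**Working it through.** The plan gives no figure for the number of questionnaires, so there is nothing to reproduce. The check is a count from the stated schedule.

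**Inputs**
- Interventions per IAMT participant: 1 + 9 = 10, which agrees with 2 per week × 5 weeks = 10 (Study design).
- Interventions per placebo participant: 1. Per heat participant: 1 (Study design).
- Stated timing: one form before each intervention (Study design).
- Group size: minimum 60, allocated 1:1:1 (Participants; Study design), so 60 / 3 = 20 per group. The count below assumes this number and no dropout.

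**Forms per participant if the timing rule is followed literally**

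| Group | All short forms | Before first treatment | After first treatment |
|---|---|---|---|
| IAMT | 10 | 1 | 10 − 1 = 9 |
| Placebo | 1 | 1 | 0 |
| Heat | 1 | 1 | 0 |

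**Does the count depend on the reading?** The form asks about changes, and a separate baseline questionnaire exists. It may therefore start only with the nine further sessions. The totals would then be 9, 0 and 0. The last column is the same under both readings, so the follow-up result does not depend on which is meant.

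**Group totals after the first treatment**
- IAMT: 20 × 9 = 180.
- Placebo: 20 × 0 = 0.

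**End of the course.** The tenth form is handed out before the tenth session. No form is stated after the full course, even in the IAMT group.

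**Do other sections supply the missing time points?** The Measurements section places its questionnaire at baseline. The Abstract and Study design set test visits for both long-term groups in weeks 3 and 5. Study design names those visits and the questionnaire in one sentence, but attaches the questionnaire to interventions and not to the visits. No other section of the visible text gives the form to the control group during follow-up.

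**After the fix.** With the form at weeks 3 and 5 in both groups, each participant has 2 common follow-up records: 20 × 2 = 40 per group.

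**The case against.** The strongest reply is that the schedule may be complete in material we cannot see. The sentence cites Figs. 1 and 2, and the second is a SPIRIT figure, which commonly sets out assessments by time point. The text does not say that the form is given only before interventions, and a journal article often leaves the detailed form schedule to the full protocol. This stands as a limit on certainty. It does not remove the point: the text states a rule, and that rule gives the control group no follow-up form. If the figures say otherwise, text and figures disagree and the text needs correcting.

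Several stronger readings are tempting, and the document does not support them:

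- A reader might infer that the perceived outcomes cannot be compared between groups at all. The Measurements section plans a baseline comparison of all three groups; only follow-up is affected.
- A reader might infer that no group reports anything after the first session. The IAMT group has nine later forms on the same schedule. What is not stated is a same-day form after treatment.
- A reader might take the totals of 10, 1 and 1 as fixed. They are one reading of the text.
- A reader might assume that training deviations are collected to explain tissue changes, or that they are an outcome. The article says neither. Statistical analysis does not name them among the participant characteristics it lists, and Aims does not list them as an outcome.
- A reader might say that a long-term comparison with placebo is promised for the perceived outcomes in particular. In Aims the comparators are written for shear motion. The broader support is in Study design, which makes the placebo group the control for the long-term effects of IAMT without limiting this to one outcome.

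It is also fair to say that these are the last-listed secondary outcomes of a pilot. No primary outcome or physical measurement is affected.

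**Conclusion.** The point holds for follow-up. On the visible text, an IAMT participant has nine short forms after the first treatment and a placebo participant has none, about 180 against 0 at 20 per group without dropout. Change in perceived flexibility and back state therefore has no concurrent control, no form follows the tenth IAMT session, and training deviations over the five weeks are known in one group only.

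The conclusion assumes that the stated timing is applied literally and that Figs. 1 and 2 do not add control-group forms. If they do, what remains is a wording correction. The matter should be settled before data collection because the loss could not be recovered, but it leaves the primary outcomes intact.

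**What to change.** 1. In Study design, state questionnaire time points that are common to the compared groups. Give the same form, including the training-deviation items, to the IAMT and placebo groups at the existing week 3 and week 5 test visits.
2. Base the between-group comparison of perceived outcomes on these common visits, with the baseline questionnaire as the starting value. The forms before each IAMT session can stay as a description of the course within that group.
3. Check Figs. 1 and 2 against the text and make them agree.
4. Optionally, add a same-day form after the first treatment in all three groups, if a short-term comparison of perceived change is wanted.

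The cost is a few minutes per participant at visits that already take place. One limit remains: the placebo group is untreated after its first session, so the added forms give a concurrent control but do not equalise the attention received over the five weeks. The report should say so.

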**Fig. 1 Fig1:**
[figure not shown]
Schematic representation of the pilot study design

**Fig. 2 Fig2:**
[figure not shown]
SPIRIT-Figure

### Informed consent, ethics approval, and confidentiality

Prior to commencing this pilot study, subjects will be informed verbally and in writing about the procedure and the aims of the study, and they will provide informed consent. All data collected, including images and videos, will be anonymised and saved on a password-protected USB drive. Individual data will not be accessible by third parties, and they will only be published anonymously. This pilot study has received ethical approval from the German Sport University Cologne (no. 80/2017) in accordance with the latest version of the Declaration of Helsinki.

### Blinding

Participants in the placebo group will assume that they have received appropriate treatments and will be informed about the placebo treatment only after this pilot study is finished. All treatments will be performed by one therapist, while all outcome measures will be assessed by another, blinded investigator. All measurements will be carried out through a standardised protocol, and they will be blind analysed a few weeks after data collection is finished.

### Participants

A minimum of 60 senior-level female soccer players aged 15–35 years, who practise at least three times a week for 90 min and are actively involved in competition, will be recruited for this pilot study. Participants must be healthy, must not suffer from chronic illness or an acute injury of the locomotor system, and must not have had back pain or any other back issue within the past 4 weeks. Because of the study investigator’s work at the elite women soccer team of Cologne, these players present a reachable collective besides their homogeneous and open-minded characteristics to evaluate the feasibility of the planned measurement protocol and generate first results on IAMT. Athletes will also be recruited from the numerous high-level women’s soccer clubs around Cologne and the German Sport University Cologne in order to achieve the desired sample size.

### Measurements

First, anthropometric data including height and weight will be obtained, and information about the athletic career, individual lifestyle, training sessions, and subjectively perceived flexibility and state of the lower back will be collected through a questionnaire to identify differences between the three groups. Skinfold thickness of the lower back will be measured using a skinfold calliper. After a 2-min rest, both sides of the body will be tested using the following order of measurements: superficial skin temperature, mechanical tissue deformation resistance (indentometry), shear motion, thickness, and compressibility of the single tissue layers, as well as flexibility of the dorsal structures. Every athlete will then receive one of the three different types of treatment and undergo post-measurements. Testing will alternate between body sides, starting with the treatment side (Figs. 1, 2, and 3). All measurements will be taken three times in a row, except for ultrasound imaging and flexibility measurements. Mean values will be used for comparative analysis.

**Fig. 3 Fig3:**
[figure not shown]
Schematic representation of the measurement points on the treatment side

### Preparing and positioning the participants

Participants will undress to their underwear, and the lumbar region and any body part receiving measurements will be cleaned and marked (Fig. 3). All measurements will be conducted with the participant in a prone position on a horizontal treatment table (Stockholm, Clap Tzu GmbH), except for flexibility testing. For all treatments, the treatment table will be pivoted into a 45° roof position to prestretch the myofascial tissue. The anterior superior iliac spine (ASIS) will be positioned above the rotation axis between the lower and mid-section of the therapy table. The participant will lie on the treatment table facing the floor, with arms lying next to the upper body, legs stretched out, and feet supported by a 10-cm-long, half-round foam roller.

### Outcomes

#### Feasibility evaluation

The evaluation of feasibility will investigate the time economy and expressiveness of the measurement methods used in terms of quality and quantifiability. In this context, it will also be determined whether all the measurements are required for further investigations. Therefore, the results of the ultrasound techniques will be compared with the already more established methods to analyse their dependability and accuracy. Shear motion analysis will be compared with the more established flexibility tests and the analysis of compressibility with the mechanical tissue deformation resistance (indentometry). Furthermore, the ultrasound measurements will be assessed by the investigator in terms of their qualitative presentability and their related analysis procedures regarding to their manageability by using a five-level Likert-type scale (from very good to very bad) after each measurement. All measurement methods will be evaluated for their time economy by measuring the time needed for each measurement process. Also, the measuring instruments used will be critically ranked by the therapist and the investigator using a five-level Likert-type scale (from strongly agree to strongly disagree). The ranking will be based on the recorded outcomes to evaluate whether they are suitable to assess short-term and long-term changes in the selected treatments and at the chosen measurement time points. Afterwards, both experts will be asked for suggestions to optimise and adapt the study protocol.

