#### Ultrasound scan

For the ultrasound measurements (Sonido Smart Plus, Zimmer MedizinSysteme), the medial aspect of a linear 3.8-cm-long transducer will be placed longitudinally 2 cm lateral to the lumbar spinous processes, midway between lumbar vertebrae (L) 2 and L3 (Fig. 3). Measurements will be taken using a cine-loop technique with a single ultrasound beam focused on the thoracolumbar fascia with a 3.2 cm depth. During the measurement, the therapy table will pivot into the 45° position at a speed of 3°/s. The thickness of the single tissue layers in the starting and end position, as well as the shear motion between these positions, will be measured in millimetres (mm) [19, 20, 24]. The compressibility of the lumbar structures will be measured in the starting position using a force gauge attached to the transducer. An ultrasound image will be taken while applying 0, 5, and 10 Newtons (N) (± 0.25) of force onto the transducer and a measurement of the thickness of each single tissue layer will be taken in millimetres [22].

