### Statistical analysis

Statistical analysis will be performed with SPSS Statistics 25 (IBM). Usual descriptive statistics will be used to summarise the results. Means per group, mean differences between the groups will be outlined with standard deviation, 95% confidence interval, minimum, and maximum. Baseline sample characteristics of the groups will be compared by using a single factor analysis of variance or in case of missing assumptions with the Kruskal-Wallis test. Qualitative variables like experiences in myofascial self-treatments and “preferred free leg” will be analysed by using a chi-squared test. Main outcomes like shear motion (distance in mm) and flexibility (range of motion in degree) will be analysed for the three measurement time points in the short-term evaluation as well as for all measurement time points of the IAMT group and the control group in the long-term evaluation by using a longitudinal generalised linear mixed model. Those analyses will include groups, time (measurement time points), and group by time interaction as fixed effects, each participant as random effect, and a covariance structure that provided the best fit for the model to obtain estimates of slopes before and after the treatment and compared between groups like age, experiences in myofascial self-treatments, and “preferred free leg”. The Kruskal-Wallis test will be used to compare the experts ranking of suitability of the measuring instruments, whereas the time economy of the measurement instruments used will be analysed by using a single factor analysis of variance, if the necessary assumptions will be met. To evaluate the quantitative expressiveness of the ultrasound measurements with those of the flexibility tests and the indentometry, their relationship will be analysed by Pearson’s correlation coefficient, if the outcomes will be distributed normally, otherwise Spearman’s correlation coefficient will be applied. The significance level for all tests will be 5%.

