## Discussion

To the best of the author’s knowledge, this proposed pilot study will be the first investigation to assess the feasibility and the quantitative impact of IAMT for the lower back on both structural and functional levels. The primary aims will be to evaluate the measurement methods used in terms of time economy and expressiveness and to create a basis to justify the sample size of future full studies.

The comparison of the ultrasound examinations with the previously more established indentometry and flexibility tests should provide information about the qualitative and quantitative properties of the novel ultrasound techniques especially in terms of their dependability and accuracy. Those results, in combination with the time economy and evaluation of the experts, are supposed to verify whether all the used measurements are necessary for future full studies.

To classify and quantify potential therapeutic effects of IAMT, possible confounding factors of the intervention, such as increased local blood flow and resulting tissue reactions or a therapist effect will be controlled by the heat group and by the attention and care the therapist gives to the placebo group. Modern and innovative techniques of ultrasound imaging initial and specific determination of thickness, compressibility, and shear motion of the single tissue layers might make it possible to examine the structural and functional properties of myofascial tissue after IAMT. These novel results may crucially provide a greater understanding of myofascial therapy, especially in IAMT of the lower back, and the potential impact of such therapy on myofascial chains. Moreover, the results may shed light on the mechanisms behind the effects of IAMT on the myofascial tissue and on the functional properties of the human body, for example, receptor stimulation or release of adhesion and fibrosis. This would allow for a better understanding of the benefits of IAMT and its subjectively perceived effects.

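### The planned correlations can show convergent validity only, not the dependability and accuracy of ultrasound that the protocol says they will analyse

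*Protocol article*

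**What the plan says.** The Aims make the quality and quantifiability of the measurement methods part of the primary outcome. Feasibility evaluation then states that "the results of the ultrasound techniques will be compared with the already more established methods to analyse their dependability and accuracy". It pairs shear motion with the flexibility tests and compressibility with indentometry. The Discussion repeats the aim, expecting information on the "qualitative and quantitative properties of the novel ultrasound techniques especially in terms of their dependability and accuracy". It adds that these results, taken with time economy and the experts' evaluation, "are supposed to verify whether all the used measurements are necessary for future full studies".

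Statistical analysis gives the method. "To evaluate the quantitative expressiveness of the ultrasound measurements with those of the flexibility tests and the indentometry", the plan is that "their relationship will be analysed by Pearson’s correlation coefficient, if the outcomes will be distributed normally, otherwise Spearman’s correlation coefficient will be applied". A 5% level applies to all tests. The other feasibility items are Likert ratings and timings.

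On repeats, the Measurements section says: "All measurements will be taken three times in a row, except for ultrasound imaging and flexibility measurements". Study design has every player tested before, immediately after and 45 min after a treatment given on the right side only. Measurements has both sides tested.

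**The concern.** Dependability means that a repeated measurement gives the same answer. Accuracy means closeness to a reference value of the same quantity. A correlation with a different quantity in different units is evidence on neither. A low value may reflect a noisy ultrasound measure, a noisy comparator, or two tissue properties that are only loosely related. A moderate value can coexist with poor repeatability or with large systematic error.

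This bears on a primary feasibility conclusion. The pilot is meant to tell a full study which measurements to keep, and ultrasound shear motion is the primary effect measure. Followed as written, the plan could support a noisy measure because it tracks flexibility somewhat, or count against a repeatable one because it captures something else.

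**Working it through.** The article gives no target correlation, reliability figure or power calculation, so there is no stated figure to reproduce.

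**Inputs from the protocol article**
- At least 60 players allocated 1:1:1, so 60/3 = 20 per group (Abstract, Study design).
- Three same-day tests, right side treated (Study design), both sides measured (Measurements).
- 5% level (Statistical analysis); taken here as two-sided, which the article does not state.
- Shear motion in mm, and layer thickness in mm at 0, 5 and 10 N (Ultrasound scan). Range of motion in degrees (Flexibility tests). Force in N at 9 and 10 mm depth and at the pain threshold (Indentometry).

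**Assumed, not in the article:** comparator reliability 0.9; true correlations 0.3 to 0.9; ICC 0.8.

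**1. Does r identify dependability?** The attenuation formula is r_obs = ρ_true × √(R_us × R_comp), so R_us = (r_obs/ρ_true)² / R_comp. With r_obs = 0.40 and R_comp = 0.9:

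| Assumed true correlation | Implied ultrasound reliability |
|---|---|
| 0.45 | 0.88 |
| 0.5 | 0.71 |
| 0.6 | 0.49 |
| 0.7 | 0.36 |
| 0.9 | 0.22 |

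One observed value fits an excellent or a very poor measure. Conversely, an ultrasound measure with reliability 0.95 gives only 0.3 × √(0.95 × 0.9) = 0.28 if the two quantities truly correlate at 0.3.

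**2. Does r identify accuracy?** Pearson's r is unchanged when one variable is rescaled or shifted in the same direction. In a simulated set of 60, replacing each ultrasound value x by 2x + 5 left r at 0.399. Nor can agreement be computed between mm and degrees, or between thickness and force.

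**3. What would significance mean?** The smallest significant r is t/√(df + t²).
- n = 60: 2.002/√(58 + 2.002²) = 0.254, and 0.254² is 6.5% shared variance.
- n = 20: 2.101/√(18 + 2.101²) = 0.444.

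At n = 60, an r of 0.40 has a Fisher-z 95% CI of 0.16 to 0.59.

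**4. What could the same-day tests give?** For a one-way ICC with n players and k tests, F = (1 + (k−1)ICC)/(1 − ICC). The limits are (F_L − 1)/(F_L + k − 1) and (F_U − 1)/(F_U + k − 1), where F_L and F_U are F divided and multiplied by the relevant 97.5% F quantiles. With ICC 0.8 and k = 3, F = 2.6/0.2 = 13.
- Placebo group, n = 20: F_L = 13/2.086 = 6.23 and F_U = 13 × 2.333 = 30.3, so 0.64 to 0.91.
- Untreated left side, n = 60: F_L = 13/1.533 = 8.48 and F_U = 13 × 1.586 = 20.6, so 0.71 to 0.87.
- Standard error of measurement (SEM) in the placebo group, with 20 × 2 = 40 df: 95% factors √(40/59.34) = 0.82 and √(40/24.43) = 1.28, that is −18% to +28%.

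**The case against.** The strongest defence is that the article claims less than its wording suggests. Statistical analysis speaks only of a relationship and labels it quantitative expressiveness, and the keep-or-drop judgement also draws on timing and expert opinion. A separate analysis plan might add a reliability analysis. This does not remove the mismatch: Feasibility evaluation and the Discussion both say that the comparison informs dependability and accuracy, and an added ICC elsewhere would not make that statement right.

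The defence does rule out several stronger readings that a reader might infer.
- *That repeat data are collected and left unused.* The same-day shear-motion values enter the longitudinal mixed model. They are simply not assigned to reliability.
- *That the trial yields no measurement error at all.* The residual of a model with a participant random effect carries test-to-test error for shear motion. It is not presented as a reliability result.
- *That a significant correlation certifies ultrasound as dependable.* No such pass mark is stated. The 0.254 threshold shows only how little significance would mean if it were read that way.
- *That both pairs are equally mismatched.* Compressibility and indentometry both record deformation under load at nearly the same site beside L2/L3, so convergence is a reasonable expectation there. It is less so for shear motion and joint range.
- *That only one ultrasound recording is made per test.* The article exempts ultrasound from triplicates but does not say how many recordings are taken.

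**Conclusion.** The point holds as a mismatch between stated aim and stated method. The correlations can support convergent validity, more plausibly for compressibility with indentometry than for shear motion with flexibility. They establish neither dependability nor accuracy, and no accuracy claim is possible because no reference for the same quantity is measured. The size depends on assumed reliabilities and true correlations: over the range shown, r = 0.40 leaves ultrasound reliability anywhere between 0.22 and 0.88. The weakness touches one primary feasibility conclusion, not the randomised comparison, and should be corrected before that conclusion is drawn.

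**What to change.** 1. In Feasibility evaluation, Statistical analysis and Discussion, describe the correlations as convergent validity. Compute them on baseline values, one pair per participant, and report them with 95% CIs. Do not use significance as evidence of dependability.
2. Assess dependability by ICC, SEM and smallest detectable change (1.96 × √2 × SEM) for shear motion, thickness and compressibility, per tissue layer, from the placebo group's before, immediately-after and 45-min tests.
3. As a sensitivity analysis, repeat this on the untreated left side of all 60 players. This assumes no contralateral effect, which is open to doubt because the Background describes the fascia as linking both sides of the body.
4. Drop the word accuracy.

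The cost is wording and a short additional analysis of data already planned, with no new visits. Re-reading stored loops would separate out reading error, but it is optional extra work and not needed for the fix. The main drawback is interpretive. Between the tests lie elapsed time, maximal flexion testing, the prestretched position and, in the placebo group, sham contact. The estimates are therefore same-day test-retest stability, probably overstating pure measurement error, and the interval with 20 players is fairly wide.
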